#### Secondary endpoints

Intraoperative T_1_, T_2_, T_3_, and T_4_ cerebral oxygen metabolism-related indexes (*rSO*_*2*_*, Da-jvO*_*2*_*ml/L, CERO*_*2*_*%*);Incidence of CDE (≥ *20% reduction in cerebral oxygen saturation relative to baseline or absolute rSO*_*2*_ ≤ *55%*);MMSE scores 1d before and 1, 3, and 7d after surgery and the incidence of DNR;1d preoperatively (baseline) and 1d postoperatively: serum neuron-specific enolase (NSE) and interleukin-6 (IL-6) levels;Time to awaken from anesthesia;Postoperative admission rate to ICU;The all-cause mortality rate at 30 days postoperatively (*follow-up*);Pulmonary complications after surgery (*bronchospasm, atelectasis, exacerbation of chronic lung disease, infection, prolonged mechanical ventilation, and respiratory failure*);Duration of the hospital stay;Presence of postoperative adverse events (*nausea, vomiting, hypotension, bradycardia, and excessive sedation*): ①A 20% reduction in systolic blood pressure relative to baseline or MAP < 65 mmHg is defined as a perioperative hypotensive event; ②Heart rate < 50 beats/min is defined as bradycardia; ③Level of sedation assessed using the Ramsay scale (*Level 1 awake*: the patient is anxious, restless or irritable; *Level 2 awake*: the patient is cooperative, well-oriented or quiet; *Level 3 awake*: the patient responds only to commands; *Level 4 sleep*: the patient is responsive to tapping between the eyebrows or strong vocal stimuli; *Level 5 sleep*: the patient is unresponsive to tapping between the eyebrows or strong verbal stimuli; *Level 6 sleep*: the patient does not respond to tapping between the eyebrows or strong verbal stimuli), where a Ramsay level ≥ 3 is defined as excessive sedation.

(**T**_**0**_: Immediately after entry, before any treatment **T**_**1**_: 15 min after tracheal intubation **T**_**2**_: 60 min after pneumoperitoneum **T**_**3**_: 120 min after pneumoperitoneum **T**_**4**_: suture completion, end of surgery).

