### Operating method

In this study, we will use a FORE-SIGHT regional oximeter (CAS Medical Systems, Inc.) to collect rSO_2_. This regional oximeter monitors intracerebral rSO_2_ using NIRS and reflectance oximetry, displaying absolute rSO_2_ values and trends. Absolute oximetry values will be defined as rSO_2_ measured with an oximetry probe calibrated with a fixed arterial-to-venous blood ratio. In our study, only absolute oximetry data will be extracted and analyzed. We will install NIRS sensors on each side of the patient's forehead and measure rSO_2_ in both brain hemispheres. Baseline rSO_2_ will be recorded before the start of any medication and before induction of anesthesia, and subsequent rSO_2_ measurements will be recorded every 10 s until the last surgical suture is complete. At the end of the procedure, the data for the entire test cycle will be read via a memory stick through the USB port on the instrument. Moreover, the data collected (within the first two hours of surgery) will finally be presented as a line graph with data visualization software (GraphPad Prism) to visualize the temporal trend of changes in rSO_2_ in both hemispheres. Although we will perform dynamic acquisition of rSO_2_ values throughout the procedure for each patient, the visualization will be limited to 2 h after the start of the procedure due to the substantial variation in the time of the procedure between patients. The absolute change in percent change in rSO_2_ will be calculated by subtracting the baseline rSO_2_ value (T_0_) from the value measured at the end of the procedure (T_4_), multiplied by 100%. The investigators will collect rSO_2_ data from the sensors placed on the patient's left and right forehead.

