### Sample size calculations

According to data previously reported by our institution, rSO_2_ values at wakefulness range from 60 to 80% for elderly patients with NFBF, consistent with previous studies [69]. Although the earlier studies of cerebral oxygen monitoring did not address the point of "NFBF," we obtained the same rSO_2_ interval in the preoperative awake state, which does not mean that this discussion is meaningless. However, the natural state of elderly patients with NFBF may not be significantly different from the average population due to the body's compensation, but when entering the general anesthesia and surgery state, the lack of cerebrovascular self-regulatory reserve capacity and the regional cerebral microcirculatory disorders of these patients only become apparent with the intensification of the systemic stress response and the increase of hemodynamic fluctuations.

Interestingly, a "15%" change in rSO_2_ values at the end of surgery relative to baseline values in both groups is considered clinically significant [70]. However, we need to state that "15%" is a research inference made for the anti-Trendelenburg position, and the laparoscopic colorectal surgery in this study was the Trendelenburg position. Due to the apparent position difference, we cannot ignore the secondary changes in cerebral perfusion and CBF. Continuing to choose the "15%" cutoff may overestimate the effect on the intervention group. Therefore, we used the more conservative "10%" relative change as the clinically significant margin in our trial. A baseline rSO_2_ of 60% to 80% was used, and the absolute change in rSO_2_ from baseline to the end of surgery was assumed to be 0% in the control group according to the pilot study and 8% in the intervention group (a 10% increase from baseline rSO_2_ of 80%). The sample-size calculation for the test of difference was performed with the use of PASS 15.0.5 software, and the total sample size needed for an unpaired t-test was calculated to be 68 at a two-sided significance level of 5% and 90% power. Considering the loss of a follow-up rate of 10%, our final sample size will be 76 (evenly distributed between the two groups).

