### Statistical analysis

Data will be analyzed using Statistical Package for Social Science 25.0 software. The Shapiro–Wilk test is used to test the normality of continuous variables, expressed as means and SDs if they are normally distributed and as medians and interquartile ranges if they are non-normally distributed. Baseline, Intraoperative, and postoperative indicators between the intervention and control groups are analyzed by t-tests, Mann–Whitney U test, chi-square test, continuous corrected chi-square test, or Fisher's exact test (Table 3). All primary and secondary outcomes analysis will be based on intention-to-treat (ITT) which means all patients who accept randomization will be included in the final statistical analysis, regardless of whether they received the intended intervention. We will also conduct per-protocol (PP) analysis for primary and secondary outcomes. ITT analysis usually attenuates differences between two groups, and PP analysis exaggerates differences between two groups. We will explore the consistency of ITT and PP analysis results and verify the results' reliability if they are consistent in the end. For the primary outcome, linear regression models will be used to generate unadjusted effect sizes with 95% confidence intervals. Preoperative baseline and intraoperative data are also included in the linear model to generate adjusted effect sizes and 95% confidence intervals. The analysis of repeated measures (rSO_2_, Da-jvO_2_, CERO_2_) will be performed using generalized estimating equations (GEE), with patient code (ID) as the within-subject variable, time as the between-subject variable, and rSO_2_, Da-jvO_2_, and CERO_2_ as the dependent variable. The ACE-R scores of the intervention and control groups will also be analyzed by GEE. What we need to be clear is that we will not adjust for multiple comparisons of secondary outcomes at numerous measurement time points, and we will focus on the separate effects of intervention because these results are exploratory. The incidence of CDE and DNR between the intervention and control group will be analyzed by the chi-square test, continuous corrected chi-square test, or Fisher's exact test. The serum NSE and IL-6 concentrations between the intervention and control groups are analyzed by covariance (ANCOVA) analysis, and the least-squares mean (LSM) difference and 95% CI will be estimated. Postoperative adverse events will be analyzed using the safety analysis set, which refers to patients who received at least one intervention in their group. Postoperative adverse events are categorical data, and the chi-square test, continuous corrected chi-square test, or Fisher's exact test will be used for statistical analysis.

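### The GEE for rSO2 at T1–T4 does not use the recorded T0 value, and the role of the preoperative MMSE in the cognitive GEE is unstated: a small loss of precision in exploratory analyses

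*Protocol article*

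**What the plan says.** **rSO2.** The Secondary endpoints section lists "Intraoperative T_1_, T_2_, T_3_, and T_4_ cerebral oxygen metabolism-related indexes", with rSO2 among them. The Statistical analysis section then says "The analysis of repeated measures (rSO_2_, Da-jvO_2_, CERO_2_) will be performed using generalized estimating equations (GEE"). It gives patient code as the within-subject variable, time as the between-subject variable and each index as the dependent variable. T0 is neither a covariate nor subtracted.

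**T0 is available.** Under Operating method, "Baseline rSO_2_ will be recorded before the start of any medication and before induction of anesthesia". The primary outcome subtracts it from the T4 value.

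**Baselines elsewhere in the same paragraph.** The adjusted linear model for the primary outcome takes in preoperative baseline data, and NSE and IL-6 are analysed by ANCOVA.

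**Cognition.** The endpoint is "MMSE scores 1d before and 1, 3, and 7d after surgery", together with the incidence of DNR. The GEE sentence for cognition refers to ACE-R scores, a scale named nowhere else in the article, and gives no time points or covariates.

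**Status.** The section calls the secondary results at multiple time points exploratory and leaves them unadjusted for multiplicity.

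**The concern.** A patient's awake rSO2 is likely to predict that patient's rSO2 during surgery. If the model leaves it out, the between-patient variation it explains stays in the error. A chance T0 difference between arms also carries into T1, T2, T3 and T4 in the same direction, so four shifted contrasts may look like four consistent observations.

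There is also a problem of coherence. The T4 reading is analysed twice: as T4 minus T0 in the primary comparison and as a raw level in the GEE. The two effects can differ only because the arms differed by chance at T0, and in a trial of 76 patients such a disagreement would be awkward to explain.

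For cognition, a reader cannot tell which scale is modelled, or whether the preoperative score is a response, a covariate or unused.

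**Working it through.** **1. The plan's own figures.** The calculation uses a "two-sided significance level of 5% and 90% power", a control change of 0 and "8% in the intervention group (a 10% increase from baseline rSO_2_ of 80"%), so the planning difference is 8 points. The article says "the total sample size needed for an unpaired t-test was calculated to be 68". No SD is stated. A t-test calculation returns 34 per arm, 68 in total, for an SD of the change between about 9.88 and 10.02. Then "Considering the loss of a follow-up rate of 10%, our final sample size will be 76": 68/(1 − 0.10) = 75.6, which rounds up to 76, or 38 per arm. Neither figure is disputed here; 38 per arm and 8 points are used below.

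**2. Assumptions.** The Sample size calculations section gives awake rSO2 as 60 to 80%. Read as mean ± 2 SD, the T0 SD is 5 points; read as mean ± 1 SD, it is 10. The documents give no correlation rho between T0 and later values, so 0.3 to 0.7 is shown. Equal SDs at T0 and T1–T4 are assumed.

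**3. Chance difference at T0 and the shift it causes.** SE = SD × √(2/38). The 95% range is ±1.96 × SE. Given a T0 difference d, the expected shift in each raw contrast is rho × d.

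| T0 SD | SE | 95% range of d | shift, rho 0.5 | shift, rho 0.7 |
|---|---|---|---|---|
| 5 | 1.15 | ±2.2 | ±1.1 | ±1.6 |
| 10 | 2.29 | ±4.5 | ±2.2 | ±3.1 |

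At SD 5 the shift is 1.1/8 = 14% to 1.6/8 = 20% of the planning difference.

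**4. GEE at T4 against the primary effect.** With complete data and time-specific group effects:

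raw T4 contrast = (T4 − T0) contrast + T0 contrast.

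The two differ by exactly d. At SD 5 that gap has a 95% range of ±2.2 points, or 2.2/8 = 28% of the planning difference. The gap is larger than the shift in step 3 because the change score also moves, in the opposite direction, by (1 − rho) × d.

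**5. Precision.** Adjustment for T0 multiplies the variance at one time point by 1 − rho². For the mean of T1–T4 under exchangeable correlation, the variance factor is (v − rho²)/v with v = (1 + 3rho)/4.

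| rho | variance factor, one time point | SE reduction, one time point | SE reduction, mean of T1–T4 |
|---|---|---|---|
| 0.3 | 0.91 | 5% | 10% |
| 0.5 | 0.75 | 13% | 23% |
| 0.7 | 0.51 | 29% | 39% |

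**6. Simulation.** For each rho, 2,000 trials with no treatment effect were simulated (38 per arm, SD 5). The patient mean of T1–T4 was compared by least squares, with and without T0. The robust GEE standard error itself was not simulated.

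| | rho 0.5 | rho 0.7 |
|---|---|---|
| SD of estimate, raw | 0.91 | 1.01 |
| SD of estimate, adjusted | 0.72 | 0.61 |
| Correlation with T0 difference, raw | 0.62 | 0.79 |
| Correlation with T0 difference, adjusted | about 0 | about 0 |
| Type I error, raw | 5.0% | 5.5% |
| Type I error, adjusted | about 4.7% | about 4.7% |

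**7. Outcomes without a baseline.** Da-jvO2 and CERO2 are calculated at T1–T4 only. The jugular bulb catheter is placed after induction, so they have no T0 value to adjust for.

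**The case against.** The strongest objection is that the article condenses a fuller plan and that the covariates of a secondary model are commonly left to the SAP. The GEE sentence does not even name treatment group, so it can hardly be a complete specification, and no sentence excludes T0. This limits the severity. It does not dispose of the point: the paragraph names this model's elements, fixes the rSO2 outcome times at T1–T4, and states baseline handling for the primary outcome and ANCOVA for the serum markers. Naming T0 here would be in keeping with the rest of the section.

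Three stronger readings are tempting and are not supported.

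- A reader might infer that the unadjusted GEE is biased or produces false positives. Randomisation keeps the contrast unbiased, its standard error already allows for chance imbalance, and the simulated type I error is near 5%.
- A reader might infer that the cognitive GEE omits the preoperative score. The endpoint lists that score as one of its time points, so it may enter as a response. Its role is unstated, which is different from absent.
- A reader might take 28% of the planning difference as the error in the GEE estimate. It is the 95% limit of the gap between two estimators; the expected shift in the GEE contrast is rho times the T0 difference.

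Also, a shift common to all four points leaves group-by-time contrasts unchanged. The protocol assigns the display of rSO2 over time to a line graph of the first two hours, under Operating method and in the Discussion. Baseline rSO2 is listed in Table 3, so an imbalance would at least be visible.

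**Conclusion.** The point holds for rSO2 as a matter of efficiency and coherence. The GEE as described leaves out a baseline that the trial records. The cost is a standard error at one time point that could be about 13% to 29% smaller at rho 0.5 to 0.7, and a common shift with a 95% range of about ±1.1 to ±1.6 points at an assumed T0 SD of 5 (±2.2 to ±3.1 at SD 10). The SD is inferred from a stated range and rho is assumed, so these figures are indicative.

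For cognition, the naming of ACE-R is a plain inconsistency with the MMSE endpoint, and the handling of the preoperative score needs stating. Da-jvO2 and CERO2 are unaffected. The primary comparison already uses T0 and is not in question. Severity is minor, since these are exploratory secondary analyses.

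**What to change.** - In the rSO2 GEE, keep T1–T4 as the outcome times and enter T0 rSO2 as a covariate.
- In the cognitive GEE, replace ACE-R with MMSE, enter the preoperative MMSE as a covariate, and use days 1, 3 and 7 as the outcome times.
- Leave the Da-jvO2 and CERO2 models without baseline adjustment and say why.
- In the same edit, name treatment group and its interaction with time, which the GEE sentence omits.

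This takes one covariate per model and a few lines of analysis text, with no new data, visits or patients. It should be settled before the allocation is decoded, so that adjustment cannot appear to have been chosen after seeing the results.

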## Discussion

We will conduct a prospective, single-center, single-blind RCT to assess the effects of interventions on rSO_2_ in patients undergoing laparoscopic colorectal cancer surgery. We will use the absolute change between postoperative and preoperative rSO_2_ values as the primary outcome of the study. Four-time points, T_1_, T_2_, T_3_, and T_4_, are selected to record real-time rSO_2_ and to perform the blood gas analysis and calculations of metabolism-related indicators of cerebral oxygenation. We plan to promptly adjust intraoperative PaCO_2_ and pH on the blood gas results. Notably, the previous clinical focus of hypercapnia has always been on the acidosis and subsequent hyperkalemia that it causes, but one study reported no significant clinical association between hypercapnia and hyperkalemia [77]. In addition, we will dynamically monitor the changes in blood gas parameters at four intraoperative points to ensure trial safety and compliance with ethical guidelines.

On the other hand, the observation of indicators related to cerebral oxygen metabolism and the examination of preoperative and postoperative levels of brain injury markers (NSE and IL-6) provides a further exploration of the comprehensive mechanism of action of PHC to improve the overall cerebral oxygenation function and exert cerebral protective effects. Notably, the majority of previous RCTs on brain protection and postoperative cognition have focused on older adults with good underlying brain function and have used "a history of cerebrovascular accident and/or cognitive dysfunction" as the main exclusion criteria, suggesting that the potential typical beneficiary group of the trial results could not be verified and limiting the externality of the clinical results and contradicting the pragmatic trials currently advocated in the world. Therefore, this study is undoubtedly a potent supplement.

In addition, during the first two hours of the procedure, we will visualize the trend of changes in cerebral oxygenation through the cerebral oxygen monitor to reflect further how the effect of PHC on rSO_2_ changes over time: whether the trend is increasing or decreasing or whether it shows irregular and dynamic fluctuations.

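### The GEE sentence for rSO2, Da-jvO2 and CERO2 swaps the roles of patient and time and names no group term; it is wrong as written and should be corrected, although only exploratory secondary analyses depend on it

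*Protocol article*

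**What the plan says.** In the protocol article, Secondary endpoints lists "cerebral oxygen metabolism-related indexes" (rSO2, Da-jvO2 and CERO2) at T1, T2, T3 and T4. The Discussion confirms that these four points "are selected to record real-time rSO" and to take the blood gases behind the two derived indexes. Every patient therefore contributes up to four values of each variable.

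For these outcomes the Statistical analysis section chooses GEE "with patient code (ID) as the within-subject variable, time as the between-subject variable", with the three indexes "as the dependent variable. The ACE-R scores of the intervention and control groups will also be analyzed by GEE". The part of the sentence that sets out the model lists ID, time and the dependent variables. It does not list the randomised group or a group-by-time term.

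Three other statements set the context:

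- On secondary outcomes at multiple time points, the same section says "we will focus on the separate effects of intervention because these results are exploratory". No multiplicity adjustment is planned for them.
- The primary outcome is handled separately: "For the primary outcome, linear regression models will be used to generate unadjusted effect sizes with 95% confidence intervals".
- The sample size comes from an unpaired t-test on the primary outcome, "calculated to be 68 at a two-sided significance level of 5% and 90% power".

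**The concern.** In a GEE, the subject variable defines the clusters within which observations may be correlated, and the robust standard error is built by summing over those clusters. Here the natural cluster is the patient. Time indexes the repeated readings inside a patient, and the between-subject factor is the randomised group. The sentence gives the within-subject role to the patient and the between-subject role to time, and leaves group out.

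Taken at face value, time point becomes the clustering unit. There would be four clusters. Readings from different patients at one time would be grouped together, while readings from one patient would fall in different clusters and be treated as unrelated. The standard error would then miss the variation between patients, which is the main source of uncertainty in a comparison of two randomised groups.

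These outcomes carry real aims. The Anticipated results section calls the chain from hypercapnia through cerebral oxygenation to cognition a critical objective and rests it partly on Da-jvO2 and CERO2. The Discussion wants to show how the effect on rSO2 develops over time. A group-by-time term addresses that second aim directly, and none is named.

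**Working it through.** **The plan's own figure.** The article gives no number for the GEE analyses. Its only related figure is the sample size: 68, or 76 after 10% loss. It states no SD. With a difference of 8 points, two-sided 5% and 90% power, the exact unpaired t-test gives totals of 46, 56, 68, 82 and 98 for SD 8, 9, 10, 11 and 12. SD 10 returns 68 (power 90.2%), and 68/(1 − 0.10) = 75.6, rounded up to 76. SD 10 is used below only as a convenient scale; the rejection rates do not depend on it.

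**Inputs**

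- From the article: 68 evaluable patients, 34 per group; 4 times (T1–T4); two-sided 5%.
- Assumed, because the article gives neither: SD 10, and the same correlation ρ between any two readings on one patient, taken as 0.3, 0.5 and 0.7.
- Model: outcome on group plus time, independence working correlation, no true group effect, Wald test at 1.96, 2,000 simulated trials per ρ. The group term had to be **added**, because the sentence does not contain one.

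**Simulation results for the group effect**

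| ρ | Empirical SD of estimate | Mean SE, cluster = patient | Type I error | Mean SE, cluster = time | Type I error |
|---|---|---|---|---|---|
| 0.3 | 1.70 | 1.64 | 6.1% | 0.81 | 38% |
| 0.5 | 1.88 | 1.88 | 5.6% | 0.69 | 49% |
| 0.7 | 2.15 | 2.10 | 5.2% | 0.54 | 63% |

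Ratio of the two mean SEs: 0.81/1.64 = 0.49, 0.69/1.88 = 0.37, 0.54/2.10 = 0.26.

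**Check by hand.** Let d_t be the difference in group means at time t. In this balanced design the estimated group effect is the average of the four d_t.

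- True variance: SD² × (2/34) × (1 + 3ρ)/4. At ρ = 0.5 this is 100 × 0.0588 × 0.625 = 3.68, so the SE is 1.92.
- Robust variance clustered on time: Σ(d_t − mean d)²/4². Its expectation is SD² × (1 − ρ) × (2/34) × 3/16. At ρ = 0.5 this is 100 × 0.5 × 0.0588 × 0.1875 = 0.55, so the root is 0.74.
- The patient-level variation cancels from the second expression. It measures only how much the group difference moves between times, so it shrinks as ρ rises while the true variance grows.
- The statistic behaves as a t with 3 degrees of freedom, so the false-positive rate is P(|t₃| > 1.96 × time-clustered root/true SE). The thresholds are 1.96 × 0.879/1.672 = 1.03, 1.96 × 0.743/1.917 = 0.76 and 1.96 × 0.575/2.135 = 0.53. The rates are 38%, 50% and 63%, in line with the simulation.

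**Reading the text for the group term.** The sentence that sets out the model omits group. The next one applies the same method to scores of the two groups, linked by the word also, and the one after says the focus is on intervention effects. A between-group comparison is intended; the model as listed does not contain the term that would deliver it.

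**The case against.** The strongest reply is that this is a slip of terminology. The method chosen exists to handle correlation within patients, the sentence is introduced as an analysis of repeated measures, and patient ID is named as an identifier. An analyst could well enter ID as the subject variable despite the wording. That reading fits the text as well as the literal one, and under it the standard errors are sound. So a reader might infer that the trial will report invalid standard errors, but the article does not establish that. The error rates above are conditional on literal execution.

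A reader might also infer that the repeated-measures analyses will not test the intervention at all. The surrounding sentences contradict this, and every rejection rate quoted here needed a group term to be put in.

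It can fairly be added that the outcomes are secondary and called exploratory, that the time trend is also to be shown as a graph, and that an article may leave detailed model terms to a fuller document. This limits the consequences and means that the missing group term alone would be a weak point. It does not excuse the reversed roles: the article chose to fix them and fixed them wrongly, so any correct later plan would have to contradict it.

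**Conclusion.** The point holds as a specification error: the roles of patient and time are reversed, and group and group-by-time are not named although intervention effects are the stated target. It is wrong as written, and should-fix rather than must-fix.

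The size is conditional. If the labels were executed literally with a group term added, a nominal 5% test would have a type I error of about 38–63% for ρ from 0.3 to 0.7, against about 5–6% when clustered on patient. The range rests on the assumed correlations, equal correlation across times, 68 complete patients and an independence working correlation. A single figure such as 63% would describe only the top of that range.

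The reach is limited to the exploratory repeated-measures analyses. The primary outcome is analysed by linear regression and the sample size by an unpaired t-test; neither depends on this sentence.

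**What to change.** Replace the GEE sentence with wording such as:

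*GEE with patient ID as the subject variable, time (T1–T4) as the within-subject variable, and group, time and group × time as model terms; the group difference at each time will be reported with its 95% CI.*

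The cost is one sentence of analysis text, best changed before the data are unblinded so that there is no doubt which model was prespecified. It needs no new data, no extra patients and no change to the primary analysis.

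Naming a working correlation, using a small-sample correction to the robust standard errors, or adding the T0 value as a covariate for rSO2 are reasonable options but not part of the correction. Ordinary robust standard errors clustered on patient already gave 5.2–6.1% type I error in the check.

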### Protocol amendment

The clinical registration of this trial was 9/15/2022, but in the follow-up protocol design, we identified several problems that needed further refinement and modification. The modified protocol will be more consistent with clinical practice, and the clinical feasibility and significance will be further expanded. In addition, we have completed the amendments of the information in the clinical trial registration platform. The amendments are described below:①In the original registration, we defined the four intraoperative time points for special attention as T_0_-T_3_ and did not specify the method to refer to the baseline rSO_2_ time point. The preoperative baseline rSO_2_ measurement time point is now defined as T_0_, and the four intraoperative time points are changed to T_1_-T_4_ to more clearly and more intuitively define the reference measurement;②In the inclusion criteria listed in the clinical registry, we added "massive intraoperative hemorrhage; intraoperative severe subcutaneous emphysema; operative time < 2.5 h, or > 4 h" as exclusion criteria, which should be an intraoperative contingency to discontinue the trial rather than preoperative screening criteria. In addition, we must clarify several discontinuation conditions in this trial: massive intraoperative hemorrhage; intraoperative severe subcutaneous emphysema; operative time < 2.5 h or > 4 h; CDE; Intraoperative change to open operation; Other events that could threaten the patient's safety;③Regarding the sample size, our calculation method remains unchanged, but the clinically meaningful threshold value of the calculation has been changed from the previous "15%" to a more conservative "10%" and the final sample size was increased from 48 to 76 cases. The specific reasons will be described in the sample size calculation;④Through the pilot trial, we found that the use of postoperative cognitive function assessment methods must be combined with the clinical reality, and the application of the Montreal Cognitive Assessment (MoCA) is challenging. Although the sensitivity of MMSE in detecting mild cognitive impairment is not good enough, it has high clinical practicability. As a secondary outcome measure, we can accept the limitations of the MMSE. Therefore, we will finally choose the MMSE scale as the tool for postoperative cognitive function assessment;⑤The previous description of "Absolute Difference" in the outcome of the main study is not appropriate. We will redefine it as "Absolute Change", that is, the actual increase or decrease between the observed value and the baseline value. The replacement of this term will not affect the rest of the experimental protocol.

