The MMSE is one of the most influential and popular international screening instruments for cognitive impairment, covering time, place orientation, immediate memory, attention, computation, short-term memory, language, and visuospatial structure skills. However, a capping and learning effect exists for the MMSE. The MMSE is insensitive to subtle changes in cognitive function that may occur after surgery. Thus, the MMSE is more suitable for preoperative screening in PND studies. The MoCA covers a broader range of cognitive domains than the MMSE, which makes it seems to be more accurate and sensitive than the MMSE for the determination of mild cognitive impairment. But our previous pilot study showed that the MoCA is too difficult and time-consuming to implement. Therefore, we will choose the MMSE as the assessment tool for postoperative cognitive function outcome (The patients with postoperative MMSE score ≤ 23 and a decrease of more than 2 points from the baseline value were defined as DNR). In addition, as a secondary outcome measure, we can accept the limitations of the MMSE.

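### The only longitudinal analysis of cognition is written for ACE-R, a scale the trial does not administer; the sentence should name the MMSE.

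*Protocol article*

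**What the plan says.** All references are to the protocol article.

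- **Statistical analysis.** The outcomes listed for repeated-measures modelling are three oxygenation variables: "The analysis of repeated measures (rSO_2_, Da-jvO_2_, CERO_2_) will be performed using generalized estimating equations (GEE"). The next sentence adds one cognitive outcome: "The ACE-R scores of the intervention and control groups will also be analyzed by GEE".
- **Statistical analysis, other routes.** Postoperative indicators in general are compared between groups by t-test, Mann–Whitney or categorical tests. For the binary cognitive outcome the section says: "The incidence of CDE and DNR between the intervention and control group will be analyzed by the chi-square test", with continuity-corrected and exact alternatives.
- **Secondary endpoints.** The cognitive endpoint is "MMSE scores 1d before and 1, 3, and 7d after surgery and the incidence of DNR".
- **Protocol amendment, item 4.** The MoCA is given up as impractical and "we will finally choose the MMSE scale as the tool for postoperative cognitive function assessment".
- **Measurement of PNDs.** The choice is repeated: "Therefore, we will choose the MMSE as the assessment tool for postoperative cognitive function outcome". Table 2 schedules the MMSE at one preoperative and three postoperative visits and lists no other cognitive scale.

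**The concern.** The analysis text and the data collection text name different instruments. The protocol commits to a longitudinal model for a score that nobody will record. The score that will be recorded at four visits has no longitudinal model named for it.

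This is not a matter of detail left to a separate analysis plan. The document does state an analysis, and states it for the wrong scale. Nor is it superseded wording: the sentence stands in the operative Statistical analysis section, and the instrument replaced by the amendment was the MoCA, not ACE-R.

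What is at stake is prespecification of a secondary outcome. If the mismatch is noticed only once scores are available, the choice between a GEE of the MMSE, separate tests at each day and the DNR comparison becomes a choice made with data in hand. The same section plans no multiplicity adjustment for secondary outcomes at the various time points. Cognition is also the last link of the mechanism (PHC to cerebral oxygenation to cognition) that the Background and Anticipated results sections say the trial will examine.

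**Working it through.** No plan figure has to be reproduced; the check is a reading of every mention of a cognitive instrument.

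**Step 1. Where each instrument is named.**

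| Place in the protocol article | ACE-R | MMSE |
|---|---|---|
| Inclusion criteria | no | yes (entry threshold) |
| Protocol amendment, item 4 | no | yes (chosen in place of MoCA) |
| Secondary endpoints | no | yes (four time points) |
| Measurement of PNDs and Table 2 | no | yes |
| Anticipated results | no | yes |
| Discussion | no | yes |
| Abbreviations | no | yes |
| Statistical analysis | yes (once, under GEE) | no |

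ACE-R is therefore scheduled at 0 visits and analysed by GEE. The MMSE is scheduled at 4 visits and named in 0 repeated-measures analyses. The figures could not be seen, so this is a check of the text and tables.

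**Step 2. What remains for the MMSE if the text is followed literally.**

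- GEE: rSO2, Da-jvO2, CERO2 and ACE-R. The MMSE is not included.
- General two-group tests for postoperative indicators: these can take the MMSE scores, one day at a time.
- DNR, which is derived from the MMSE: categorical test of incidence.

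So the MMSE keeps an analysis, but not a repeated-measures one.

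**Step 3. Amount of data concerned.** The sample is 76 patients, 38 per group, with three postoperative MMSE assessments each: 76 × 3 = 228 planned postoperative scores before any loss to follow-up. This is a count of the data that the sentence fails to reach. It does not measure bias or loss of power.

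**Step 4. What the GEE sentence would carry over.** The word *also* ties the cognitive GEE to the preceding description. That description names patient ID, time and the dependent variables, but no group term. Changing the instrument name alone would leave the comparison of groups implicit.

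**The case against.** The strongest reply is that this is one wrong word. Only one cognitive scale is administered, and the sentence sends the cognitive scores of the two groups to GEE, so the intention to model the MMSE by GEE is plain. **This stands.** ACE-R is very probably a slip, and nothing suggests that the authors meant to leave the MMSE without a longitudinal analysis. The sentence is still wrong as written and should be corrected before the scores are analysed.

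The second reply concerns importance. The Statistical analysis section calls the secondary results exploratory, and the Discussion says the trial was not designed to quantify the relation between hypercapnia and cognition. **This also stands** and keeps the point modest.

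A reader might go further in three ways that the document does not support.

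- **That cognitive inference would rest only on an unadjusted binary outcome.** The general t-test and Mann–Whitney provision for postoperative indicators still covers the MMSE as a score.
- **That the DNR definition is itself an error.** The rule, "postoperative MMSE score ≤ 23 and a decrease of more than 2 points from the baseline value were defined as DNR", is worded to the same effect in the study design section, so there is no contradiction. Any rule that joins an absolute cut-off to a decline asks for a larger fall from a higher baseline. The authors acknowledge the limits of the MMSE and accept them for a secondary outcome. A different threshold or a second DNR tabulation would be a preference.
- **That the GEE is the principal cognitive analysis.** The protocol does not rank its cognitive analyses.

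**Conclusion.** The point holds in limited form. The Statistical analysis section assigns its only longitudinal analysis of cognition to an instrument that the trial does not collect, and it omits the one that it does. As written, that GEE has no data, and the MMSE scores fall back on general two-group tests and the DNR comparison.

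The size is small to moderate: one secondary, exploratory outcome, with up to 228 planned postoperative scores lacking a named longitudinal model. The primary rSO2 analysis and the sample size are not touched. The conclusion rests on the text and tables shown. The judgement that ACE-R stands for MMSE is an inference, though a strong one, because no other cognitive scale is scheduled.

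A separate clerical matter: Table 2 and the accompanying text under Measurement of PNDs list DNR at the preoperative visit, where it cannot occur under its own definition. No analysis depends on this.

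**What to change.** Replace the ACE-R sentence in the Statistical analysis section with:

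*MMSE scores at days 1, 3 and 7 will be analysed by GEE with patient as subject, terms for group, day and group × day, and the preoperative MMSE as covariate.*

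The bare minimum is to substitute MMSE for ACE-R. The fuller sentence is worth the extra words because it states the group comparison explicitly and uses the baseline score that is already collected.

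The cost is one sentence. Visits, data collection, sample size and clinical management do not change. The correction should be made and dated before the cognitive scores are analysed. The preoperative DNR entry can be removed from both Table 2 and the text beside it in the same edit.
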